# Multicentre Pilot Study to Evaluate the Efficacy of Targeted Exercise in Combination with Cytisinicline on Smoking Cessation at 12 Months: MEDSEC-CTA

**DOI:** 10.3390/healthcare12242516

**Published:** 2024-12-12

**Keywords:** tobacco use cessation, cytisine, exercise, randomised controlled trials as topic

## Abstract

**Background/Objectives:** Current scientific evidence shows both the relationship between good physical condition and a lower incidence of certain chronic diseases (including smoking), as well as the efficacy of cytisinicline. The aim of this protocol is to evaluate the efficacy of the synergistic effect of the combination of targeted physical exercise, together with brief advice and taking the drug cytisinicline, to achieve smoking cessation. **Methods**: We propose an experimental, multicentre, randomised, controlled study with two parallel arms to be carried out by a multidisciplinary team in the primary care setting of the Andalusian public health system (APHS) in Spain, with a follow-up of 12 months. The population sample will include people who are aged between 18 and 65 years and meet the criteria to be eligible for treatment with cytisinicline financed by the APHS: smokers of 10 or more cigarettes per day who are in the determination/action phase for smoking cessation of the transtheoretical model of Prochaska and Diclemente, willing to start anti-smoking treatment imminently and confirmed, with high dependence to nicotine (Fagerström’s test ≥ 7), with a motivation to quit smoking according to the Richmond test (≥6), and who have made a previous smoking cessation attempt in the last year. The study consists of two treatment arms. EXPERIMENTAL ARM: Smokers who are going to be prescribed targeted physical exercise and brief advice to stop smoking while receiving cytisinicline treatment (1.5 mg tablets) according to the care process. CONTROL ARM: Smokers will receive a standard leaflet explaining physical exercise to the general population and brief advice on smoking cessation when starting cytisinicline treatment, according to the care process. The calculated sample size is 75 participants per arm. **Results:** The primary results will allow us to estimate the efficacy of prescribing physical exercise as an adjuvant therapy to classic multicomponent treatment, incorporating it as an additional element to be considered when it is accepted by the smoker. **Conclusions:** This protocol (NCT06579846) evaluates the efficacy of combining physical exercise, brief advice, and cytisinicline to support smoking cessation, improve fitness, and reduce smoking-related comorbidities

## 1. Introduction

Increasing importance is being given to the so-called “physical exercise prescription”. Proof of this is the recent specific plan implemented in Andalusia, Spain [1]. Current scientific evidence shows the relationship between good physical fitness and reduced incidence of certain chronic diseases, ranging from “some evidence of reduced disease rates in the case of lung disease (with few studies conducted)” to “good evidence” for hypertension and “excellent evidence” for reduced disease rates in obesity, coronary heart disease and all-cause mortality [2,3].

Smoking can be considered a chronic, addictive disease with a tendency to relapse. It has associated comorbidity, such as multiple cancerous processes, chronic obstructive pulmonary disease, and other pathologies that also constitute important cardiovascular risk factors, such as hypertension and obesity [4,5]. In this respect, obesity is a common barrier that smokers, especially women, often cite as a reason for delaying quit attempts. It is therefore interesting to consider adjuvant therapy that also helps to control risk factors, such as the prescription of physical exercise, in people who decide to quit smoking. This may also be useful for dealing with the withdrawal syndrome caused by smoking cessation. In this regard, a meta-analysis published in 2023 indicates that short interventions with physical exercise are effective in reducing craving and withdrawal symptoms in smokers, as well as helping to improve their mood [6]. In the same vein, a clinical trial to test the efficacy of a 12-week exercise intervention in conjunction with health education interventions also shows greater reductions in craving while attenuating the negative emotional effect that is generally associated with craving [7]. Cytisinicline is a recently financed drug by the Spanish Health System to help quit smoking, increasing the demand to cope with this addiction [8,9,10]. In this sense, the aim of this protocol is to evaluate the efficacy of the synergistic effect of the combination of targeted physical exercise, together with brief advice and taking the drug cytisinicline, to achieve smoking cessation.

## 2. Materials and Methods

### 2.1. Study Design

A multicentre, randomised and controlled experimental study with two parallel branches, to be carried out by a multidisciplinary team of different specialties (medicine, pharmacology and physical education sciences) of the Maimonides Institute of Biomedical Research of Cordoba (IMIBIC), in the field of the Andalusian Public Health System (APHS), is proposed.

### 2.2. Study Population

The study population will be made up of people who smoke and who are assigned to different health centres in the Health District of Cordoba and Guadalquivir, belonging to the APHS. This Health District has a total population of 437,883 users. The health centres to be included in the study are: “Aeropuerto” (15,496 users), “Carlos Castilla del Pino” (serving 21,533 users), and “Bujalance” (4537 users), including patients between 18 and 65 years old [11]. The study population will be composed of individuals aged 18 to 65, drawn from the 19.7% of the Andalusian population who smoke [12].

### 2.3. Sample Size

In order to calculate the sample size, we have taken into account the results obtained in four experimental studies very similar in objective, intervention and time of evolution to ours [13,14,15,16]. One [13] was discarded because it did not have results 12 months after the start of the intervention.

An aggregation of results weighted by sample size yielded a difference between the control and experimental groups of 3.18% smoking cessation at 12 months. For a delta of 5%, an alpha of 5% in a hypothesis of superiority, and a beta error of 20%, a sample size of 289 participants per branch was obtained. As it was not feasible to recruit such a large number of patients, we set a target of 75 patients per arm (150 in total), performing a sensitivity analysis, if no differences were found, to check if they were not found for reasons related to the sample size.

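### The abstract calls 75 per arm the calculated sample size although the calculation gave 289, and 289 fits its stated superiority inputs only at a control quit rate of about 2 to 4%

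*Protocol article*

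**What the plan says.** Section 2.3 pools earlier trials of similar interventions. The pooling "yielded a difference between the control and experimental groups of 3.18% smoking cessation at 12 months". The section then gives the design inputs, "For a delta of 5%, an alpha of 5% in a hypothesis of superiority, and a beta error of 20" percent, and reports that "a sample size of 289 participants per branch was obtained". Because that number could not be recruited, "we set a target of 75 patients per arm (150 in total").

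The abstract reports only the smaller number, and describes it differently: "The calculated sample size is 75 participants per arm".

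Section 2.3 gives no control-arm quit rate and no sidedness. It does not say whether the 5% is the difference to be detected or a margin to be exceeded.

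**The concern.** There are three linked problems.

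- **The label.** The abstract presents as the output of a calculation a number that replaced that output, at 75/289 = 26% of its size. Someone who reads only the abstract will take the trial to be powered at 75 per arm.
- **The 289.** For a difference between two proportions, a 5-point gain with 289 per arm is enough only when both rates are very low (or, by symmetry, very high). In the abstract and section 2.11, every control participant receives cytisinicline and brief advice, and section 2.4.1 requires motivation to quit. A 12-month control rate of 2 to 4% would at least need to be stated.
- **The 5% beside the 3.18%.** Neither meaning of delta fits a superiority hypothesis with an expected difference of 3.18 points.

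What is at stake is what the trial can claim. A reader may take 289 as the adequate size and judge the shortfall from it, or carry it into a later definitive trial.

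**Working it through.** **Inputs from section 2.3:** delta 5 points, alpha 0.05, power 0.80, expected difference 3.18 points (direction not stated, taken here as favouring exercise), 289 per arm reported, 75 per arm adopted. **Assumed, because not stated:** the control rate p1, shown over a range; one- and two-sided tests both tried.

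**Step 1. Can 289 be reproduced as a superiority test of 5 points?** With p2 = p1 + d and p̄ = (p1 + p2)/2,

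n per arm = [z_α √(2p̄(1−p̄)) + z_β √(p1(1−p1) + p2(1−p2))]² / d².

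Solving for n = 289 with d = 0.05, two-sided, gives p1 = 2.36%:

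[1.960 × 0.3041 + 0.8416 × 0.3020]² / 0.0025 = 0.8502² / 0.0025 ≈ 289.

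One-sided (z_α = 1.645), the solution is p1 = 3.76%. The mirror solutions lie above 91%. Variants do not move the result far: the control rate needed is 1.6 to 3.0% with a continuity correction, 2.6 to 4.1% with the arcsine formula, and 1.3 to 3.2% if 289 includes 10 to 20% dropout.

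**Step 2. What would other control rates need?** At p1 = 10%, two-sided:

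[1.960 × 0.4677 + 0.8416 × 0.4664]² / 0.0025 = 1.3092² / 0.0025 = 685.6, so 686.

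| Assumed control rate | n per arm, 5 points, two-sided | one-sided | n per arm, 3.18 points, two-sided |
|---|---|---|---|
| 5% | 435 | 343 | 955 |
| 10% | 686 | 540 | 1,590 |
| 15% | 906 | 714 | 2,147 |
| 20% | 1,094 | 862 | 2,627 |
| 25% | 1,251 | 986 | 3,029 |

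**Step 3. Delta against the expected difference.** If 5 is a superiority margin, the distance to be shown is 3.18 − 5 = −1.82 points, so the expected effect lies inside the null hypothesis. Power is Φ(−0.0182/SE − 1.645). At p1 = 10% and 75 per arm, SE = √[(0.0900 + 0.1144)/75] = 0.0522, giving Φ(−1.99) = 2.3%. Over control rates of 10 to 25% it stays below 3% at 75 and at 289 per arm, and a larger sample lowers it. If 5 is a target difference, it is 5/3.18 = 1.57 times the pooled estimate.

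**Step 4. Another route to 289.** Adding the two figures in a non-inferiority-type formula gives a distance of 8.18 points:

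n = (z_α + z_β)² [p1(1−p1) + p2(1−p2)] / 0.0818², with p2 = p1 + 0.0318.

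- One-sided 5%, p1 = 17.9%: 6.183 × 0.3133 / 0.006691 = 289.5.
- One-sided 2.5%, p1 = 12.8%: 7.849 × 0.2459 / 0.006691 = 288.4.

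**Step 5. What 75 per arm delivers** (two-sided 5%):

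| Assumed control rate | Power, 5 points | Power, 3.18 points | 95% CI half-width (true difference 5 points) | Difference detectable at 80% power |
|---|---|---|---|---|
| 10% | 15.0% | 8.8% | 10.6 points | 17.8 points |
| 15% | 12.4% | 7.5% | 12.1 points | 19.6 points |
| 20% | 11.0% | 6.8% | 13.3 points | 20.9 points |
| 25% | 10.1% | 6.4% | 14.3 points | 21.8 points |

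The half-width is 1.96 × √{[p1(1−p1) + p2(1−p2)]/75}.

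**The case against.** The control rate is the decisive input and is not in the article. It may stand in the full protocol or in the trials that were pooled, and a condensed article may leave out such detail. The omission alone would be no finding. Nor can the 289 be called wrong outright: it does follow at a control rate of about 2 to 4%, and the range of 10 to 25% is an assumption of this review. This stands, and it limits the point to a mismatch that the authors must resolve.

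It is also fair that 289 drives nothing. Section 2.3 gives it up openly, the title says pilot, and the limitations section names sample size first. That lowers the practical harm, but it does not make the abstract's sentence correct or explain the 5% beside the 3.18%.

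Three stronger readings are tempting, and the documents do not support them:

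- A reader might infer that 289 is impossible at any plausible quit rate. The article gives no rate against which to judge that.
- A reader might infer from Step 4 that a non-inferiority formula was used by mistake. That would contradict the stated superiority hypothesis, but two different settings give the same number, so the origin is conjecture.
- A reader might infer that a later trial with 289 per arm is bound to fail. At the assumed rates it would have 44 to 27% power for a true 5-point effect. That is underpowered, but failure is not certain.

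**Conclusion.** The point holds in two parts that need no outside assumption, and one that is conditional.

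- **Certain:** the abstract contradicts section 2.3. The calculation gave 289, and 75 is a feasibility target.
- **Certain, if the 3.18 points favour exercise:** a delta of 5% does not fit that expected difference. As a margin it cannot be met at the expected effect, and as a target difference it exceeds the evidence cited for it. If the 3.18 points favour control, the fit is worse.
- **Conditional on the unstated control rate:** as a superiority test of 5 points with 80% power, 289 per arm holds only near 2.4% (two-sided) or 3.8% (one-sided). At an assumed 5% the need is already 435 (343 one-sided), and at 10 to 25% it is 686 to 1,251 (540 to 986 one-sided). In that range the shortfall of 75 per arm is much larger than a comparison with 289 suggests.

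The sample-size statement is thus wrong as written in the abstract and unresolved in section 2.3. Nothing here shows that the enrolment target of a pilot must change.

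**What to change.** 1. In the abstract, describe 75 per arm as a feasibility target for a pilot instead of a calculated size.
2. In section 2.3, say whether 5% is a superiority margin or a target difference, and reconcile it with the 3.18%.
3. State the control quit rate and sidedness that were used, and recompute the 289 for a superiority test on those inputs. The table in Step 2 is a sensitivity range and should not be copied in as the corrected number.
4. State what 75 per arm delivers, as a range under assumed control rates of 10 to 25% (two-sided): power of about 15 to 10% for 5 points and 9 to 6% for 3.18 points, a 95% confidence interval half-width of about 11 to 14 points, and a detectable difference of about 18 to 22 points at 80% power.

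The cost is wording and figures only. Enrolment, visits and data collection are untouched. The downside is that the stated figures become less favourable and the trial must be presented as estimating an effect with limited precision.

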### 2.4. Sample Selection or Eligibility Criteria

#### 2.4.1. Inclusion Criteria

The sample will include people who, agreeing to participate in the study, are aged between 18 and 65 years and meet the criteria to be eligible for treatment with cytisinicline financed by the APHS. These criteria are smokers of 10 or more cigarettes per day, who are in the determination/action phase for smoking cessation of the transtheoretical model of Prochaska and Diclemente [10], willing to start anti-smoking treatment imminently and confirmed, with a high dependence on nicotine (Fagerström’s test ≥ 7), with a motivation to quit smoking according to the Richmond test (≥6), who have made a previous smoking cessation attempt in the last year, and who are covered by the APHS.

#### 2.4.2. Exclusion Criteria

The following will be causes for exclusion in this study: persons suffering from pathologies that prevent physical exercise (malignant hypertension, heart failure, hyperthyroidism, peripheral arterial disease), or other diseases that, in the opinion of the research team, contraindicate the practice of physical exercise or their participation in the study, either due to a foreseeable lack of adherence or risk of adverse events; changes in the usual treatment in the last 90 days; and inability to sign informed consent. Also, suffering from pathological processes that limit life expectancy significantly (<5 years), and the existence of contraindications established in the technical data sheet of cytisinicline [17]: pregnancy, breastfeeding, hypersensitivity to cytisinicline, unstable angina, history of recent myocardial infarction, clinically relevant arrhythmias, recent history of stroke.

### 2.5. Recruitment of Participating Smokers

Recruitment will be carried out by Family Medicine physicians in the Primary Care clinics of the aforementioned health centres of the APHS (Aeropuerto, Bujalance and Castilla del Pino). The Family Medicine physicians will be responsible for evaluating and confirming the medical conditions of the study population, based on medical records and their medical criteria.

The patient will be proposed to participate in the study in routine consultations when he/she has attended due to a desire to stop smoking and is going to receive pharmacological treatment with cytisinicline. Nursing staff from each of the health centres may participate in the recruitment process by virtue of the Resolution of 22 March 2024 of the Directorate General for Public Health and Equity in Health, which validates the “Guide for the indication, use and authorisation of dispensing of medicines subject to medical prescription by nurses: smoking cessation” [18].

The recruitment period will last 6 months, with a mid-term review after 6 months and a final review after 12 months.

### 2.6. Branch Allocation and Randomisation

To prevent some of the variables from influencing smoking cessation, adaptive randomisation will be used. This is a technique used in clinical trials that allows treatment allocation to participants to be changed over the course of the study based on the cumulative results. Unlike traditional randomisation, where treatment assignment is fixed and decided before the study starts, adaptive randomisation adjusts the probability of treatment assignment on the fly, which may increase the efficiency of the study and improve the likelihood of detecting significant differences between treatments. The first 20 patients will be randomised in a simple way, using a randomisation table. From patient 21 onwards, the composition of each of the groups will be taken into account to weigh the probabilities of falling into one group or the other.

### 2.7. Source of Data

Data will be obtained by clinical interview with the participants and, if allowed, from the patient’s digital medical history in DIRAYA (the APHS electronic medical record).

### 2.8. Data Management

The data will be collected and managed using the electronic data capture tool REDCap (Research Electronic Data Capture), a platform used in the field of independent public research, hosted on a virtual server located at the Reina Sofia University Hospital (Cordoba, Spain). This server is managed by the same technical team that manages the health data of patients at the hospital. REDCap (https://projectredcap.org/, accessed on 10 December 2024) is a secure, web-based software platform designed to support data capture for research studies, providing: (1) an intuitive interface for validated data capture; (2) audit trails for tracking data manipulation and export procedures; (3) automated export procedures for seamless data downloads to common statistical packages; and (4) procedures for data integration and interoperability with external sources.

Access to this platform will only be allowed to the researchers of this study, preventing these data from being accessed by third parties.

### 2.9. Study Variables

The data collected will correspond to the following study variables, both outcome and explanatory.

Outcome variables will be: number of cigarettes smoked daily (discrete quantitative) *; smoking cessation (dichotomous): variable calculated on the basis of whether the number of cigarettes is equal to 0, and exhaled air CO-oximetry detects a value equal to or less than 10 ppm *; blood pressure (continuous quantitative); heart rate (continuous quantitative); weight in kilograms (continuous quantitative) *; and Body Mass Index (BMI) (continuous quantitative): variable calculated on the basis of weight and height) *.

Explanatory variables are sex (qualitative polychotomous); age (discrete quantitative); occupation (qualitative); postcode of residence (qualitative); cumulative smoking (discrete quantitative) *; and physical nicotine dependence measured by the Fagerström test [19] (discrete quantitative); psychological dependence, as measured by Glover Nilsson’s test [20] (discrete quantitative); motivation to quit smoking, as measured by the Richmond test [21] (discrete quantitative); weekly alcohol consumption (Standard Drinking Units-UBE) (discrete quantitative) *; World Health Organisation (WHO) Global Physical Activity Questionnaire (GPAQ) [22] and Benisovich’s physical activity self-efficacy scale [23].

(*) Some of the outcome variables can be considered intermediate variables of other explanatory variables, due to their causal relationship.

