### 2.10. Material Used for Smoking Determination and Other Instruments

A CO-oximeter of the brand “Co Check”, sold by MD Diagnostics Ltd. (Kent, UK), distributed by Sibel S.A. (Barcelona, Spain), code 01PLS18B, with a sensitivity of 1 ppm and an accuracy (repeatability of 2%, purchased in 2023) will be used to measure smoking and smoking cessation. To differentiate between smokers and ex-smokers, the criteria established in the Andalusian Comprehensive Smoking Plan (ACSP) will be followed [24].

Regarding arterial pressure, an OMROM M6-Confort (HEM-7000-E-V) (Omron HealthCare, Kyoto, Japan) will be used for the blood pressure measurement. The height and weight (Barys Plus Ref ASI06472; Asimed, Sibel group, Barcelona, Spain) of the participants will be recorded.

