### 2.13. Statistical Analysis Plan

For the statistical analysis, the R programming language and its IDE (Integrated Development Environment) will be used: RStudio, in its most updated version.

Initially, a descriptive analysis of the baseline characteristics of the study population will be carried out using median and interquartile ranges for quantitative variables and absolute and relative frequencies for categorical variables.

To compare groups by bivariate analysis, Wilcoxon, Chi-square or Fisher tests will be used, as appropriate. Causal inference between intervention and outcomes will be made through multivariate analysis using logistic regression for the dichotomous variable “Smoking cessation” and linear regression for the variable “Number of cigarettes”, adjusting for potential confounders.

All analyses shall be conducted on an intention-to-treat basis, and no missing data shall be imputed.

Statistical significance will be established at a *p*-value < 0.05. Further analyses, including sensitivity and subgroup analyses, will be conducted to explore the robustness and generality of the findings.

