### 2.14. Bias Control

Selection bias will be controlled by applying the same selection criteria to the participants in the different groups to be compared, which will have identical monitoring. In addition, in the collection of information, a record of losses to follow-up will be kept, collecting as much information as possible about them. Regarding misclassification bias, smoking will be considered as a criterion of truth, the measurement of 6 or more ppm of CO in exhaled air by CO-oximetry. Finally, multivariate analysis using logistic regression will control for various confounding factors.

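### Participants who report no cigarettes but read 6 to 10 ppm CO are abstinent under section 2.9 and smokers under section 2.14

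*Protocol article*

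**What the plan says.** Three places in the protocol article bear on how smoking status is determined.

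- **Section 2.9 (Study Variables)** defines the dichotomous outcome by two joint conditions. The first is self-report: "variable calculated on the basis of whether the number of cigarettes is equal to 0". The second is biochemical: "exhaled air CO-oximetry detects a value equal to or less than 10 ppm".
- **Section 2.14 (Bias Control)** states, for misclassification bias, that "smoking will be considered as a criterion of truth, the measurement of 6 or more ppm of CO in exhaled air by CO-oximetry".
- **Section 2.10 (Material Used for Smoking Determination and Other Instruments)** describes the CO device, "with a sensitivity of 1 ppm", and adds: "To differentiate between smokers and ex-smokers, the criteria established in the Andalusian Comprehensive Smoking Plan (ACSP) will be followed". It gives no ppm figure.

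Section 2.13 names the cessation variable as the outcome of the logistic regression. Section 2.3 bases the sample size on cessation at 12 months, the endpoint that is also in the article's title.

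**The concern.** A binary endpoint needs a rule that gives each participant one value. Here two cut-offs stand in the current text. Nothing gives one of them precedence, assigns them different purposes (such as baseline status against follow-up status), or labels one as a sensitivity analysis.

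The participants caught between the two are those who say they have stopped and whose CO is in an intermediate range. Biochemical verification exists for exactly this group. If the question stays open until the data are in, an analyst could use either cut-off and point to protocol text in support.

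**Working it through.** The protocol gives no figure on this point to reproduce. The check is a comparison of the two rules, followed by arithmetic on what one reclassified participant is worth.

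**1. Overlap of the rules**

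Inputs: abstinent if cigarettes = 0 and CO ≤ 10 ppm (section 2.9); smoker if CO ≥ 6 ppm (section 2.14); device sensitivity 1 ppm (section 2.10), read here as whole-ppm steps.

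| Reported cigarettes | CO (ppm) | Section 2.9 | Section 2.14 |
|---|---|---|---|
| 0 | 0 to 5 | abstinent | not a smoker |
| 0 | 6 to 10 | abstinent | smoker |
| 0 | 11 or more | not abstinent | smoker |
| 1 or more | any | not abstinent | decided by CO |

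- Among participants reporting zero cigarettes, five whole-ppm values (6, 7, 8, 9, 10) satisfy both rules. No reading satisfies neither.
- With one cut-off in both sections, the overlap is empty. At 6 ppm, abstinence means 0 to 5 and smoking 6 or more. At 10 ppm, abstinence means 0 to 10 and smoking 11 or more.

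**2. Weight of one participant**

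- Planned size is 75 per arm (section 2.3), so one participant is 1/75 = 1.33 percentage points in that arm.
- The difference of 3.18 points that section 2.3 derives from earlier studies equals 0.0318 × 75 = 2.4 participants. The 5-point delta equals 0.05 × 75 = 3.75 participants.

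**3. Effect on the treatment difference**

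Let a share f of the section 2.9 quitters in each arm read 6 to 10 ppm. The document does not give f, so the range of 5% to 20% is an assumption.

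- *Same share in both arms.* The new difference is (1 − f) × the old one. For 3.18 points: 0.95 × 3.18 = 3.02 and 0.80 × 3.18 = 2.54. The change is 0.16 to 0.64 points, whatever the underlying quit rates.
- *Unequal numbers.* If k more participants are reclassified in one arm than in the other, the difference moves by k × 1.33 points: 1.33 for k = 1, 2.67 for k = 2, 4.00 for k = 3.

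**4. Possible head count**

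Quit rates under the section 2.9 rule are also assumed, from 10% against 15% up to 20% against 25%.

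- Control arm: 75 × 0.10 × 0.05 = 0.4, up to 75 × 0.20 × 0.20 = 3.0 participants reclassified.
- Experimental arm: 75 × 0.15 × 0.05 = 0.6, up to 75 × 0.25 × 0.20 = 3.75 participants reclassified.

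These counts show scale only and do not predict what will be observed.

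**The case against.** The strongest reply is that the outcome has only one definition. Section 2.9 says how the variable is calculated, section 2.13 analyses that variable by name, and section 2.14 is a single sentence in a supporting section that does not redefine the outcome. On that reading 10 ppm governs and the 6 ppm figure is a stray inconsistency. Part of this stands: the two sections are not rival definitions of equal rank, and an analyst following the plan plainly would use 10 ppm. It does not remove the conflict, because section 2.14 presents 6 ppm as the standard against which misclassification is judged. By that standard, the section 2.9 variable misclassifies everyone in the 6 to 10 ppm band.

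One could also say that 6 ppm is meant for baseline smoking status. Section 2.14 does not say so, and the inclusion criteria in section 2.4.1 contain no CO measurement.

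A reader might infer four stronger things that the document does not support:

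- *Any reading of 6 to 10 ppm counts as both quit and smoking.* It does so only with zero reported cigarettes. Anyone who reports smoking is not abstinent under section 2.9.
- *Section 2.10 adds a third, competing cut-off.* The regional plan's value is not given and may equal either figure. Section 2.10 only fails to resolve the conflict.
- *The three centres may classify differently.* Cessation is a calculated variable held in a shared database (section 2.8), and nothing says that centres assign status themselves.
- *The conflict could shift the result by about as much as the expected effect.* A change in the overall quit rate is not comparable with a difference between arms. With equal reclassification, most of the change cancels, and no reason is given to expect imbalance.

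**Conclusion.** The contradiction holds and should be corrected before outcome data are analysed. It rests on the text alone: participants reporting zero cigarettes with CO of 6 to 10 ppm have two statuses on the trial's main endpoint, and no section resolves this.

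How many participants are affected cannot be computed, since the document gives neither CO distributions nor quit rates by arm. What follows from its own figures is 1.33 points per reclassified participant at 75 per arm. If the band holds the same share of quitters in both arms, the treatment difference barely moves. With small numbers a net imbalance of three participants, or 4.00 points, would exceed the 3.18-point difference in section 2.3, but that is a possibility and not an expectation. The case for correction is therefore that the endpoint should have one fixed value per participant, not that a bias of known size or direction exists.

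**What to change.** Before any outcome data are analysed, state one CO cut-off for the 12-month cessation endpoint, together with the zero-cigarette condition. Use it in sections 2.9 and 2.14, and write the figure into section 2.10 beside the reference to the regional plan. Either 6 or 10 ppm removes the overlap; the choice is the investigators' and should be recorded with its reason. Report the other cut-off as a labelled sensitivity analysis, computed from the ppm values already collected.

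No new measurement is needed. The costs are a protocol wording amendment, which under section 2.18 needs prior ethics committee authorisation, and slightly lower quit rates if the stricter cut-off is chosen.
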